## Abstract

Pesticides use in Southeast Asia has increased steadily, driven by the growth of large-scale commercial farming, as well as a desire to maximise food production in rural subsistence economies. Given that use of chemical pesticides, such as organophosphates and carbamates, has known potential health impacts, there are concerns about the safety of agricultural workers, and a need for a better evidence base to underpin regulation and worker education. This study, undertaken in 9 districts in Lao PDR, Thailand and Vietnam, will interview agricultural workers to investigate how they use pesticides, their knowledge of risks and self-protective practices, and their self-reported illness symptoms. In each district researchers will recruit and interview 120 participants engaged in vegetable farming, who have recently used pesticides, making a total of 1080 subjects divided equally between the three study countries. Workers’ degree of pesticides exposure will be determined from acetyl cholinesterase concentrations in capillary blood samples collected using field test kits, and these data will be analysed together with the interview findings. Country findings will be compared and contrasted, and general patterns noted. Knowledge gained about risky behaviours, self-protective practices and degree of association with serious pesticides exposure will assist policy makers and inform health improvement programmes.

## Introduction

### Genesis of the project

The planned study is a comparative investigation of health impacts of pesticides use to be completed by teams from universities in Thailand, Lao PDR and Vietnam, with support from Swansea University, UK. The idea for a study of this type came from Mahasarakham University (MSU) Thailand, based on earlier work by [name] and associates [1]. A plan to include Myanmar had to be abandoned due to major internal disorder associated with the 2020 military coup, but the Myanmar research lead remains in our network team and has contributed to background research on pesticides policy and agricultural practices in Southeast Asia. ‘Seed corn’ funding for a comparative study was provided by MSU, but the schedule and scope of work was disrupted by the COVID-19 pandemic. Swansea University had been involved in early project planning, and was eventually successful in securing a UK Global Challenges Research Fund (GCRF) award to allow the project to progress. During the period covered by the original project plan, only MSU was able to conduct fieldwork, and that research is now being treated as both a feasibility and a pilot study, which will assist in the full implementation of the research plan set out below. This pilot work has been helpful in focusing work on agricultural workers, rather than continuing with the original plan to also include testing of fruit and vegetable samples sent to market, and in refining the structured interview instrument.

### Background

Pesticides are used extensively in agriculture around the world to improve crop yields by controlling insects, fungi, molluscs, and rodents [2]. Their use is especially prevalent in farming regions in Asian countries, as grains, vegetables and fruit are the main products that support families in rural subsistence economies. Chemical pest control has been utilized for centuries to increase and protect fruit and vegetable crops, and there may be resistance to changing what are seen as long-established practices [3–5]. There is also a powerful economic incentive for farmers to increase production of food as a way of increasing incomes. However, in the longer term, chemical pesticides have been shown to have harmful effects on the ecological system and there is mounting evidence of damage to human health [6–12]. Pesticides can contaminate rivers, lakes and oceans, which in turn may well pollute the natural environment and food chain. Potential risks to human health documented in the literature include: acute neurologic poisoning, chronic neurodevelopmental impairment, cancer, reproductive dysfunction, and possibly dysfunction of the immune and endocrine systems [7]. Pesticide residues on agricultural products can be transferred directly to humans, with deleterious health effects [13,14]. Moreover, both soil contamination and water contamination may also have negative health effects [15,16]. Apart from effects on health through diet, those who handle and apply pesticides may be affected, as absorption occurs through the skin, lungs and mucous membranes. Farm workers, including sprayers and mixers, are a high-risk group whose health may be seriously compromised [17].

All three countries in the study are major food producers and exporters. Large-scale commercial farming has grown in Asia in recent decades [18–20], with major impacts on subsistence farmers and local communities; this has led to a dramatic increase in pesticides use. All the countries have been affected by recent social and economic disturbances. For example, the Thai government’s attempts to guarantee rice prices for farmers led to major political turmoil, and support for small farmers remains a challenging development issue. It has been estimated that the volume of pesticides used in SE Asian countries increased by approximately 400 per cent in the first decade of the new millennium [3]. Thailand is reported to be the highest user of imported pesticides by volume in the region [21], while Vietnam has the highest application rate of 16.5kg/hectare [22]. However, analysis by these latter authors shows that the acceleration in the use of pesticides has been higher in recent years in Cambodia and Lao PDR than in Vietnam and Thailand. This is largely because, before 2000, the volumes used (kg per hectare) had remained low in Lao PDR (close to zero) and Cambodia, but had already risen in Thailand and Vietnam. Consequently, in the decade to 2012, and based on a calculation of exponential growth rates, pesticides use increased by 61% each year in Cambodia, 56% in Lao PDR, 9.8% in Vietnam and 6.8% in Thailand. Throughout this decade, each country had a different pattern of change: the use of pesticides remained low in Lao PDR, rose in most (but not all) years in Thailand, accelerated from ~2008 to 2012 in Cambodia, and fluctuated in Vietnam, peaking in 2008 and 2012 [22].

A follow-on study by the same research team found that 100% of sampled vegetable farmers in Vietnam, 73% in Cambodia and 59% in Lao PDR were ‘overusing’ pesticides in the sense of applying levels in excess of a profit-maximizing optimum [23]. It has been reported that many producers purchase pesticides without proper training regarding their application [24]. This has prompted widespread public concern about possible harm to health.

Most pesticides are synthetically-produced organic and inorganic chemical compounds, although biological agents are also coming into wider use [25]. The most commonly imported pesticides are organophosphates (OPPs) and carbamates [26]. OPPs and carbamates kill insects by blocking acetylcholinesterase (AChE), an enzyme that catalyses hydrolysis of a neurotransmitter acetylcholine, resulting in overstimulation of the neuromuscular system and the parasympathetic nervous system. Exposure to OPPs by inhalation or ingestion with or without food is toxic to the human body. It can be detected by a reduced AChE concentration in capillary blood. Acute OPP poisoning symptoms include: increased salivation, diarrhoea, vomiting, muscle tremors, gastrointestinal upset, and confusion [27]. The onset of symptoms can start within minutes or hours and last for days to weeks. In the long term, lower-dose exposure to OPPs has been reported to cause polyneuropathy and cardiovascular diseases [28]. Carbamates can also pose both health and environmental hazard, including through groundwater contamination [29] and food [29,30].

The health impact of pesticide use has been a topic of heated debate for many years in Asian countries, both at national and local government levels. There is a need to prevent adverse health effects as part of a wider pesticides management strategy, and there would be major advantages in establishing a framework for cooperation within the Association of Southeast Asian Nations (ASEAN). At present, countries in the Mekong region have only their differing national strategies, and it would be valuable to compare approaches and develop a more uniform approach that takes the best ideas from each country.

Although all three countries in the study have developed legal frameworks to regulate pesticides use, limitations on what is permissible and enforcement are generally not strict. In 2009, the Food and Agriculture Organisation of the United Nations launched a project to encourage ‘harmonisation’ of pesticides regulation in Southeast Asia [31], in which all three study countries participated and produced work plans. Currently all are signatories to the Basel (1989), Rotterdam (1998) and Stockholm (2001) Conventions, which control aspects of the transboundary movement, disposal, trade and use of pesticides. Myanmar which we hope to include in future studies, has not so far ratified the Rotterdam Convention. All continue to permit the use of organophosphates and carbamates on crops, but have introduced legislation on registration of products, licensing, import controls, and labelling requirements [see 32]. All rely on the relevant ministries to oversee pesticides use, and none have an independent agency to ensure public safety such as the United States’ Environmental Protection Agency [33]. According to a recent joint UN FAO and WHO report, there is an urgent need for improved evaluation and risk assessment to regulate pesticide residue levels in food [34].

Developing an effective policy response to negative impacts of pesticides use is a challenging task, with no single approach fitting all contexts [35]. Thailand has probably moved further than Vietnam or Lao PDR to develop a national strategy, while Vietnam has introduced an innovative pesticide tax, and there are promising training schemes for pesticide retailers in Thailand and Vietnam [22]. Thailand’s 2018–2037 strategy has identified increasing the quality and quantity of agriculture products as one of five key development targets. The strategy proposes five key principles to safeguard food quality and avoid harm: 1) farming that reflects local identity; 2) safe farming; 3) biological farming; 4) regulation of processed agricultural products; and 5) smart farming [36]. This strategy puts safety at the centre of its plan for improving agriculture products. It would transform agricultural practices so that farmers adopt animal husbandry and crop cultivation methods that do not damage the environment or human health. Regarding pesticides, sustainable agriculture requires an effective pesticide management system that follows international standards. Such a system, if developed, could provide a model for neighbouring countries and help introduce a more consistent approach to pesticide control and surveillance in ASEAN countries.

A scoping exercise for the present project found many single-country studies of agricultural workers’ pesticides use in Mekong region countries, but a paucity of comparative studies.

Interview studies that examine some combination of farm workers’ agricultural methods, pesticides and health knowledge, attitudes, health protective practices, and self-reported illnesses have been undertaken in Thailand [37–40], Vietnam [41–44], Lao PDR [45,46], Myanmar [47–49], and Cambodia [50]. A small subset of studies use field capillary blood tests to measure farm workers’ AChE levels, thus adding objective data on degree of pesticides exposure to interview findings [1,51–55]. Taken together, the single-country studies give a reasonable picture of farming practices and patterns of pesticides use across the region, but because of variations in data collection, study sample size, farm types and crops covered, and degree of rigour, further research is needed for comparative analysis.

Comparative studies that use a standardised methodology to compare the situation in more than one Mekong region country are thin on the ground. The most comprehensive study found in our preliminary review is Schreinemachers and colleagues’ 2017 research on small-scale vegetable farmers in Vietnam, Lao PDR and Cambodia [56]. The researchers utilised a researcher-administered questionnaire to gather data from 900 households in 93 villages. Questions covered knowledge, attitudes and practices (KAP) related to pesticides use as well as self-reported symptoms of pesticides poisoning. As mentioned earlier, a team with the same lead researcher has also investigated volumes of pesticides used in Vietnam, Lao PDR and Cambodia utilising a later survey of 1000 households in 93 villages in the three countries. [23]. The present study fills a gap by providing current comparative data on a different three country set of Mekong region countries. It concentrates more on health impacts, including attention to both self-reported symptoms and examination of capillary blood samples for pesticides exposure. We believe this triangulated design, based on both self-reported health status and objective blood test data, will reduce the possibility of common method bias (CMB) by using different procedures to measure dependent and independent variables [57].

## Aim and objectives

The general aim of the study is to investigate the potential health impacts of pesticides use on agricultural workers.

The specific objectives are:

To estimate the prevalence of high OPP and carbamate exposure via AChE concentrations found in agricultural workers’ capillary blood samples.To determine the proportion of workers with suboptimal behaviours that predict high exposure to pesticides.To examine workers’ health knowledge regarding pesticides-related risks, the prevalence of heath-protective behaviours, and self-reported ill health.To investigate possible associations between agricultural practices, health knowledge, health-protective practices and reports of ill-health, and the concentration of cholinesterase in capillary blood samples.

## Materials and method

### Overview of survey and blood cholinesterase assays

Our study investigates agricultural workers’ self-reported use of pesticides, health knowledge, health protective behaviours, and health status, in combination with the measurement of pesticide exposure in capillary blood samples. Direct questioning of workers is reported to be the most common research method for assessing pesticide exposure [58], as was confirmed in our own scoping exercise [1]. In our study pesticide exposure will be assessed via measured cholinesterase concentrations using commercial field test kits (see below). Empirical fieldwork will be completed in selected localities in Thailand, Vietnam, and Lao PDR, so as to facilitate comparison of the situation in the three countries.

Researchers in each country will purposively select three suitable districts within the province in which their university is located, so that fieldwork will be conducted across 9 such districts (groups of ‘villages’ or ‘local areas’), with a target of 120 interviews per district. A researcher-administered structured interview will be used to collect data on agricultural production, health knowledge, health protective practices and behaviours, and illness episodes. Pesticides exposure will be measured as AChE concentrations in agricultural workers’ capillary blood using field test kits (described below).

### Structured interviews

A researcher-administered structured interview will be used to collect data concerning the nature of agricultural work, pesticides use, workers’ health knowledge, health protective practices, and self-reported experiences of ill health. Interviews of this type are sometimes described as survey interviews or standard interviews, and contain mainly closed-end questions that resemble a questionnaire, but are typically read to the respondent and completed by the researcher. Research assistants (paid research staff or postgraduate students) will be trained to explain the meaning of the various items to workers and complete the form in their presence. The structured interview is adapted from the instrument used in a study by [name] and associates [1]. Content validity of items in that instrument were confirmed by an index of conjugate (IOC) calculation. All items had IOC scores greater than 0.5 and an internal reliability coefficient (Cronbach’s α) of more than 0.7. The original Thai interview containing 59 items has been expanded to 83 items in the instrument prepared for the present study. This was modified *inter alia* to use terms and units that apply to all ASEAN countries, to ensure that multi-choice items covered all logical possibilities, and to add additional questions regarding specific pesticides types (insecticides, herbicides and fungicides), crop types, planting periods, self-medication and medicines prescribed by healthcare professionals.

#### Measuring blood cholinesterase concentrations in agricultural workers

Exposure to pesticides can be detected by low acetyl cholinesterase enzyme (AChE) concentrations in capillary blood samples. To measure AChE, we will utilise field kits containing lancets and reactive paper test strips (AChE field test kits, lot U620164, manufactured by the Government Pharmaceutical Organisation [GPO] Thailand). Blood samples (0.2 mL/capillary) will be obtained from a lancet-punctured fingertip of participants, undertaken by volunteer assistants drawn from public health officers, nurses, paramedics, or doctors in the local area. The samples will be allowed to precipitate for 30–45 minutes, followed by the reactive paper test. After 7 minutes, changes in colour on a paper test strip will be recorded using the four categories specified on the standard instruction sheet provided by the GPO with the test kits. The categories are: normal (AChE units per ml >100); safe (87.5–99.9); at risk (75.0–87.4); and probable health impact (<75). The outcome of primary interest is probable health impact.

The blood test results will be analysed alongside the interview data to determine whether participants with AChE levels that indicate probable health impact differ in their agricultural practices, health knowledge, health-protective practices and extent of self-reported illness. We will use descriptive and inferential statistics to explore associations (if any) between key variables, in line with specialist advice on appropriate multivariate analyses.

### Survey design details

#### Sample size basis

The outcome variable for sample size considerations reflects our first objective, to determine the proportion of workers with abnormal concentrations of acetyl cholinesterase (AChE) in capillary blood samples. Recent studies of agricultural workers in Vietnam [59] and Lao PDR [60] show that about 35% of participants had high exposure to pesticides with likely health impacts, as indicated by AChE levels in capillary blood samples.

#### Sampling frame

Background inquiries in Thailand suggest that numbers of households engaged in vegetable farming in districts (villages) in the study province growing these crops for the commercial market do not exceed 200 per district. Our resources will allow us to interview 120 individuals per district (representing about 60% of households in that district), and hence obtain 360 responses from 3 districts in each country.

#### Clustering

We will interview only one person from any one household to avoid data replications on household-level behaviours, such as laundry; this also allows us to use a single intra-cluster correlation coefficient (ICC) for responses from the same district. With no ICC available from our single-district Thai pilot study, we have used the unadjusted median ICC observed in primary care studies across a range of variables: (interquartile range [IQR] 0 to 0.032) [61], and set the ICC here to 0.01. With m = 120 interviews per district, our design effect, calculated as 1+(m-1)*ICC [62] is 2.19; this compares with design effects values ~1.5, as reported in surveys of developing countries [63]. Our confidence intervals are thus inflated by a multiplicative factor of 1.48 over those based on the assumption of independent responses; this adjustment accounts only for clustering within districts (groups of villages).

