## Fieldwork process

Sampling of cases is based on purposive sampling of three groups of villages/districts in each of the three countries and subsequent recruitment of agricultural workers. The three districts (or groups of villages) will be selected so that taken together they cover a range of small and large farms and spread of vegetable crop types.

Respondents will be sampled randomly from the population of farm workers in the village/district.

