As a first step health or local government personnel familiar with the district will compile a list of workers involved in vegetable production in the village/district. The list will include all members of households aged 18 and above who work regularly as farmers. Candidates may be natives or migrant workers, but must be fluent in the main language of the study country. They will be encouraged to participate through the offer of a small reward, a cash payment of less than £1 GBP payable on completion of the study. The list will comprise information on name, large or small farm and gender. The number of households and people on the list will be noted.The research team will use a randomising procedure to select from the list 120 first choice workers’ households and 30 reserves (with the latter listed in order).The health or local government staff assisting with the project will be advised of the selection. They will approach the first 120 named candidate households selected by the research team as first choices for inclusion to ask whether a volunteer adult household member is willing to meet with the research team to discuss participation in a research project on pesticides use. Information sheets will be distributed.Those volunteering will be contacted by researchers. The content of the information sheet will be explained and opportunities to ask questions provided. Those indicating their consent to participate will be screened to determine whether they meet the study inclusion criteria (which include a check that only one member per household takes part). Those selected will sign or provide a thumb print on a consent form.The main interview will be conducted either immediately or within a few daysWhen interviews are completed, consent to take blood samples will be confirmed. Only participants who agree to both interview and blood sample will be included in the study. Capillary blood samples will be taken using finger-prick lancets. In Thailand local public health staff measure AChE levels of farm workers routinely as part of a government health promotion initiative, using test kits identical to those purchased from the Thai GPO for the study. If tests were completed within the past 4 weeks these results will be used for this study, as was the case in the pilot study. If no such data are available for consenting participants from the local health service, finger-prick blood tests will be undertaken after the interviews.In the event that candidates from the original 120 selections fail to meet the research team, are found to be ineligible or do not consent to participate in all stages of the study, additional candidates from the reserve list will be approached one by one to make up the numbers.Participants completing the interviews will be given a health protection information sheet detailing dos and don’ts of safe pesticides use.Participants completing the blood tests will be advised of where to seek help if any adverse effects (such as infection) arise. They will also be told how they will be notified of the blood test result and that local health staff will advise them on necessary treatment or behavioural change. They will be given the small study reward.

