### Analysis outline

Data will be summarised using appropriate descriptive statistics; we will report on associations between agricultural methods, health knowledge, health-protective practices, self-reported illness and blood test results.

Data from each country will be analysed separately before considering whether an analysis of pooled data is appropriate.

Description of all variables: frequencies, or ranges and measures of central tendencyCombining structured interview responses to give overall measures of: outcomes, knowledge, practices/behaviours and exposures. The variables to be combined will be listed *a priori*.Measures of ill-health, knowledge, behaviours and exposures will be described separately and together.Bivariate explorations will be used to examine the variables shown in Table 1.

**Table 1 pone.0258134.t001:** Contingency tables for each comparison.

	Ill-health measures	Exposure	Practices/behaviours	Knowledge	Cholinesterase concentration
Ill-health measures					
Exposure					
Practices/behaviour					
Knowledge					
Cholinesterase concentration					

4. Multivariate analysesPrimary outcomes: AChE concentrations, ill-health measures, separately & togetherCovariates to be tested one by oneCovariates with P<0.20 will be entered into exploratory models

a) Logistic regression: high AChE concentration, any ill-health, each health issue (modelling strategy to be based on backwards LR, -2LL, VIF, check enter model)

Predictors:

1. Behaviours
a. Likely to increase exposureb. Likely to decrease exposure2. Knowledge score3. Cholinesterase concentrations (when exploring ill-health)4. Significant covariates from one-by-one testing will include: location, SES, education, literacy (ability to write), age, gender, hours worked, distance between home and farm.

Sensitivity analyses will, in turn, exclude:

Migrant workersEarlier diagnosis of pesticide poisoning

A priori sub-group analyses:

Each countrySelf-employedLowest SES or income categoryNo formal education

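### One respondent per household still allows co-workers from the same farm, so farm identity should be recorded and used when practices set by the farm are tested

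*Protocol article*

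**What the plan says.** The Clustering section limits recruitment by household: "We will interview only one person from any one household to avoid data replications on household-level behaviours, such as laundry". It draws a consequence from this: "this also allows us to use a single intra-cluster correlation coefficient (ICC) for responses from the same district". The ICC is then fixed ("set the ICC here to 0.01") and used once: "With m = 120 interviews per district, our design effect, calculated as 1+(m-1)*ICC [62] is 2.19". The section also states a limit: "this adjustment accounts only for clustering within districts (groups of villages".

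Other sections describe who can enter:

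- Under Fieldwork process, the districts together should "cover a range of small and large farms and spread of vegetable crop types".
- The frame is a list of workers, from which workers' households are drawn at random. Migrant workers are eligible.
- On that list: "The list will comprise information on name, large or small farm and gender".
- The only exclusion for a shared unit is membership of the same household.
- Employment status is a covariate, and the self-employed are an a priori subgroup in the Analysis outline. Some respondents are therefore expected not to be self-employed.

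The Analysis outline specifies logistic regression with location among the covariates. The later multilevel model is conditional, applies to pooled data, and names farm type rather than the individual farm.

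**The concern.** The household rule removes one shared unit and leaves another. The protocol's reason for the rule is that people who share a household repeat its behaviours. The same reasoning applies to people who share a farm: products, sprayers, protective equipment and routines may be set by the farmer or employer. Two hired workers from different households can both be drawn, and for such practices they supply something nearer one observation than two.

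The objectives include finding behaviours that predict high exposure and testing associations between agricultural practices and AChE. The Reporting section says the models will identify behaviours to target. If co-workers are treated as independent and AChE results are correlated within farms, a practice fixed by the farm can be declared a predictor too often. A district term does not remove this, because the correlation acts within districts. A farm-type term does not remove it either, because two farms of the same type are still different farms.

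**Working it through.** **1. The plan's own figures.** Inputs from the Clustering and Precision sections: m = 120, ICC = 0.01, p = 0.35, n = 360.

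- Design effect = 1 + 119 × 0.01 = 2.19; square root 1.480.
- Interval = 0.35 ± 1.96 × √(0.35 × 0.65 / 360) × 1.480 = 0.35 ± 0.0729, or 27.7% to 42.3%.

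The stated 2.19, 1.48 and 28% to 42% all reproduce.

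**2. Why the prevalence interval is not the target.** A district ICC can be read as the average correlation over all pairs of respondents in the district, pairs from the same farm included. With half the sample on farms of 5 and a farm ICC of 0.2, same-farm pairs contribute 0.5 × 4 × 0.2 / 119 = 0.0034 to that average, inside the assumed 0.01.

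**3. Tests of a farm-set practice.** Let f be the share of respondents on shared farms, k the respondents per shared farm, and ICC_y the within-farm correlation of the outcome. For a practice identical across a farm:

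DE_farm = 1 + f(k − 1)ICC_y, and true error = 2[1 − Φ(1.96 / √DE_farm)].

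The documents give none of f, k or ICC_y, so every row below is an assumption. The last column simulates ordinary logistic regression with district fixed effects, for 360 respondents in 3 districts, 1500 samples per row and no true effect.

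| f | k | ICC_y | DE_farm | Error, formula | Error, simulated |
|---|---|---|---|---|---|
| 0 | 1 | 0.2 | 1.00 | 5.0% | 4.7% |
| 10% | 3 | 0.1 | 1.02 | 5.2% | – |
| 20% | 5 | 0.05 | 1.04 | 5.5% | – |
| 25% | 5 | 0.2 | 1.20 | 7.4% | 7.9% |
| 50% | 5 | 0.1 | 1.20 | 7.4% | 7.2% |
| 50% | 5 | 0.2 | 1.40 | 9.8% | 8.7% |
| 50% | 10 | 0.2 | 1.90 | 15.5% | 12.1% |
| 100% | 5 | 0.2 | 1.80 | 14.4% | 12.1% |

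The simulation sets the ICC on the latent scale, which is smaller on the observed binary scale. This is why it falls below the formula in the heavier rows. Its Monte Carlo standard error is about √(0.087 × 0.913 / 1500) = 0.7 percentage points.

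**4. Practices only partly set by the farm.** With a within-farm correlation ICC_x of the predictor, DE = 1 + f(k − 1)ICC_y ICC_x. Taking f = 35%, k = 5, ICC_y = 0.2 and ICC_x = 0.3 (assumed): DE = 1 + 0.35 × 4 × 0.2 × 0.3 = 1.084, error 6.0%. For a practice constant within the farm, DE = 1.28 and the error is 8.3%.

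**5. The upper end.** A separate simulation (4000 samples per scenario, latent-normal outcome, practice constant within farm) gave 6.1% with 20% hired, 5 per farm and correlation 0.2. It gave 18.5% with 50% hired, 10 per farm and correlation 0.4. The formula reaches 30.8% only if every respondent is on a farm of 10 with ICC 0.30.

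**The case against.** The case on the other side has five parts.

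- **Placement.** The single-ICC sentence belongs to the sample-size section, which is tied to the first objective, prevalence. It makes no claim about the regression models, and the section says that only district clustering is covered. This stands. What remains is that the farm is not named as a remaining level and no stated model term represents it.
- **The interview form.** The 83-item instrument is not shown and covers the nature of the work, so it may record farm or employer. This stands: the identifier cannot be called missing, only unstated.
- **The frame.** It counts households growing vegetables for market, at most 200 per district in the Thai inquiries, and households are drawn. Large or small farm may describe a household's own holding. If nearly all respondents work their own plots, the effect is negligible. This stands as a limit on size. It does not remove the point, since migrant workers and people who are not self-employed are expected.
- **Scores.** The plan combines interview answers into overall measures that mix individual with farm behaviours, which weakens the effect (step 4). This stands for scores, less so for single practices fixed by the farm.
- **Analysis detail.** The choice between clustered standard errors and a random intercept can be left to an analysis plan, and the models are called exploratory. True, but no analysis plan can cluster on a field that was not collected.

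**Conclusion.** The point holds in conditional form, as a cheap improvement. One respondent per household does not by itself secure independence within districts for practices set by a farm. If hired co-workers are recruited and AChE results are correlated within farms, tests of those practices may be too liberal. The error of a nominal 5% test runs from about 5% (few shared farms, or scores diluted by individual behaviours) to about 8% to 12% (25% to 50% of the sample on farms of 5 to 10, latent ICC 0.2). The size rests wholly on assumed values.

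A reader might infer more, and the documents do not support it:

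- That the P-values are too small as a matter of fact. No figure for hired workers or co-workers per farm is given.
- That the 28% to 42% interval is wrong. It reproduces, and farm correlation is nested within the district.
- That shared farms could never be identified afterwards. The interview form is not shown.
- That interviewing about 60% of households takes in most of a farm's hired workforce. The 60% refers to vegetable-farming households, not to employees of any farm.
- That false-positive rates of 15% or more are to be expected. In both simulations such rates need the extreme values of the assumptions together.

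**What to change.** 1. Unless the interview form already does so, add a farm or employer identifier (a code is enough) to the worker list under Fieldwork process and to the interview record. This has to be settled before listing and interviewing, because it cannot be recovered at analysis.
2. Report the number of distinct farms per district and how many respondents share one. If few do, the results will barely change, and the report can say so.
3. Where farms are shared, use farm-clustered standard errors, or a farm random intercept within district, in the logistic models of the Analysis outline.
4. In the Clustering section, state that the single district ICC applies to the prevalence estimate only.

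The cost is one extra field, one clustering term, and somewhat wider intervals for farm-level practices. No limit on recruitment per farm is needed.
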